#### 2.2.3. Withdrawal Criteria

Patients must be withdrawn under the following circumstances:Patient’s wish to be withdrawn from the study (withdrawal of consent).Patient is lost to follow-up.Major protocol violation considered relevant by the investigator.The protocol therapy may be discontinued if the patient is judged to be intolerant to the study drug.The patient is not able to complete the 12 months’ treatment (<80% compliance).

If, during this study, a full-blown clinical picture of dementia emerges, the patient will be treated with the therapies indicated for this pathology and prematurely discontinued from the study (drop-out) due to disease progression. The data of patients enrolled but not evaluable will, in any case, be collected and entered into the study database. Any discontinuation must be recorded in the case report form by the investigator, who will indicate the date and reason(s) for withdrawal.

## 3. Trial Design

This is a non-profit, monocentric, prospective, randomized in double-blind, controlled vs. placebo, phase IV study. Taking into account that no treatments have been so far authorized with the specific indication for the MCI, the majority of symptoms typical of MCI are those for which choline alphoscerate has obtained the marketing authorization. In view of this, we are identifying this study as a phase IV investigation. A total of 60 patients with mild cognitive dysfunction and associated vascular damage will be evaluated and randomized in a 1:1 ratio of choline alphoscerate (1200 mg/day) or placebo, for 12 months. The study duration is estimated to be 24 months for each enrolled patient: 12 months for the enrolment period, max. 21 days for the screening period, 12 months for the treatment period, and, finally, the project completion of data collection: LVLP (Last Visit Last Patient).

Patients will be informed about the objectives, procedures, and possible risks and will be asked to sign and to date the informed consent for inclusion in this study. They will be visited and assessed for inclusion and exclusion criteria. During screening, patients will undergo the following assessments:-Demographic data (age, sex).-Physical examination, vital signs, and blood pressure.-Medical history.-Intake of previous/concomitant therapies.-Laboratory tests: complete blood count with formula; AST; ALT; creatinine; glycemia; azotemia; total bilirubin; total and HDL cholesterol; triglycerides; thyroid hormones FT3, FT4, and TSH; vitamin B12; and folic acid (sampling performed within 1 month of screening will be accepted).-Electrocardiogram (ECG) (examination performed within 3 months of screening will be accepted).-MRI (examination performed within 6 months of screening will be accepted).

Cognitive functions will be evaluated through the administration of the following neuropsychological tests: Mini-Mental State Examination (MMSE); Montreal Cognitive Assessment (MOCA); Memory of the Figure of Rey; Test of Corsi; Verbal Span; Immediate and Deferred Re-enactment of Rey’s 15 words; Free and Cued Selective Reminding Test (FCRST); Clock Drawing Test; Copy of Rey’s Figure; Frontal Assessment Battery (FAB); Phonemic verbal fluency test; Semantic verbal fluency test; Attentive Matrices Test; Beck Depression Inventory (BDI); Apathy Evaluation Scale (AES); Basic Activities of Daily Living (BADL); Instrumental Activities of Daily Living (IADL); and study drug dispensation. The BADL and IADL scales will be administered to the patient’s family member/caregiver.

Baseline Visit (Visit V0) is scheduled within 3 weeks from screening. This visit might overlap with screening if all data requested for enrolment are available. During this visit, the investigator will check for compliance with the inclusion/exclusion criteria. The patients who meet the criteria will be randomized to receive the study treatment (choline alphoscerate or placebo). At the end of the visit, patients meeting the inclusion criteria will be provided with a sealed and coded small box containing the study treatment.

Visit 1 is scheduled at 3 months from baseline visit (±3 days). At this visit, for a compliance check, all used and unused containers of treatment should be returned. The patients will therefore receive choline alphoscerate/placebo for the next 3 months of treatment.

Follow-up will be carried out at 3, 6, 9, and 12 months. The evaluation will be according to the flowchart reported in Figure 1. The patient will perform MRI at enrolment and at 12 months for a detailed measurement of the levels of atrophy in the areas of interest.

### Randomization

Patients will be randomly assigned to ARM A (placebo) or ARM B (choline alphoscerate) with a 1:1 ratio. The allocation to the assigned treatment ARM will remain unknown to the patients, to the Principal Investigator and/or her delegates, and to the personnel in charge of the data management and the statistical analyses until the database lock. The randomization list will be prepared by an Independent Statistician who will collaborate with the unblended responsible for the preparation of the experimental drug for the randomization list management, using a computer random number generator. The randomization will be performed at Visit 0 (baseline), after the inclusion/exclusion criteria check.

## 4. Statistical Analysis

### 4.1. Sample Size

In accordance with the primary study objective, the estimation of sample size is based on the variation in the volume of the hippocampus. There is no study evaluating brain atrophy in MCI patients treated with cholinergic drugs. The clinical hypothesis to be verified is a reduction in hippocampal volume. This value has shown the ability to discriminate patients between AD, MCI, and the healthy control [25].

Based on this study, the mean difference in these groups was 0.7 cm^3^ with a maximum standard deviation of 0.6 [25]. Fixing α = 0.05, β = 0.05 (i.e., power = 95%), and SD = 0.6 (chosen as the higher value observed in the reference study) and conducting a two-sided t test, 42 patients (i.e., 21 patients in each arm) are sufficient for detecting a difference of 2 points in MMSE. To reduce the influence of drop-out patients on the estimate of the treatment effect size, a further 25% patients will be added. Based on these calculations, a total of 60 patients (30 in each arm) will be randomized.

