## 2. Methods

### 2.1. Objectives of Study

#### 2.1.1. Primary Objective

This study intends to evaluate the slowing and/or stabilization of atrophy of the hippocampus, entorhinal cortex, neocortex, and ventricular dilation induced by treatment with the cholinergic precursor choline alphoscerate in patients with mild cognitive dysfunction with associated vascular damage.

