### 4.3. Analysis

The treatment comparison on the difference between the two arms in the changes in brain hippocampal volume at the final visit from baseline will be performed using Repeated-Measures ANOVA.

The test will be conducted at the standard 0.05 significance level. In case of a non-normal distribution, the data will be normalized through a log-transformation. A non-parametric method will be used in case the normality will not be observed after the data transformation.

The treatment effect will be estimated in terms of the difference in changes at the final visit from the baseline between the two treatments, and the corresponding two-sided 95% Confidence Interval (CI) will be provided. All the secondary endpoints will be analyzed according to their standard methods. All the statistical methods will be detailed on the Statistical Analysis Plan which will be finalized before the database freezing. Statistical analysis of the safety data will address the safety population. No method for replacing missing values will be applied, and all the missing datapoints will be removed from analysis according to pairwise exclusion. The MedDRA dictionary will be used for coding AEs. AEs will be summarized by the System Organ Class (SOC) and Primary Preferred Term (PPT). They will also be stratified by seriousness and relationship with the study treatment. All abnormalities noted on the physical examination at enrolment and during this study will be descriptively analyzed as the frequency distribution. Previous and concomitant medications will be coded using the WHO dictionary with the ATC codes. Concomitant diseases at study entry will be coded with the MedDRA dictionary. These data will be descriptively analyzed as frequency distributions.

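### The 95% power in section 4.1 is not established for the primary test: its inputs describe a gap between diagnostic groups, not a between-arm difference in 12-month change

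*Protocol article*

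**What the plan says.** Section 4.1 bases the sample size on variation in hippocampal volume and acknowledges that no study has evaluated atrophy in MCI patients given cholinergic drugs. It then turns to a reference study of hippocampal volume: "This value has shown the ability to discriminate patients between AD, MCI, and the healthy control". From that study it takes its two inputs: "the mean difference in these groups was 0.7 cm^3^ with a maximum standard deviation of 0.6". The error rates are set by "Fixing α = 0.05, β = 0.05 (i.e., power = 95%), and SD = 0.6", and the result is that, "conducting a two-sided t test, 42 patients (i.e., 21 patients in each arm) are sufficient". The effect named as detectable at the end of that sentence is 2 MMSE points. Adding 25% for drop-out, the article arrives at 60 randomised patients, 30 per arm. The hypothesis is described only as a reduction in hippocampal volume.

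The primary objective (section 2.1.1) is to "evaluate the slowing and/or stabilization of atrophy of the hippocampus, entorhinal cortex, neocortex, and ventricular dilation". The primary analysis (section 4.3) is a repeated-measures ANOVA of "the difference between the two arms in the changes in brain hippocampal volume at the final visit from baseline", and the effect is to be reported as the between-arm difference in change with a two-sided 95% confidence interval. Section 3 places MRI at enrolment and at 12 months.

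**The concern.** The quantity powered and the quantity tested differ in kind. A mean gap between diagnostic groups compares how large the hippocampus is in people with different conditions. The primary test compares how much volume is lost over one year in two arms of patients who all have MCI.

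Both inputs are affected. First, a treatment that slows or stabilises atrophy can at most prevent the loss that would have occurred on placebo. A 0.7 cm3 effect would therefore need placebo patients to lose at least 0.7 cm3 in one year, which is the whole mean gap quoted between diagnostic groups, and the drug to prevent all of it. Second, the spread of volumes between people is not the spread of within-person change.

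This is the only power justification for the primary comparison. A reader of a null result would credit the trial with a 95% chance of having found the effect, when that figure was never derived for the comparison made.

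**Working it through.** **Inputs from the article.** Difference 0.7 cm3, SD 0.6, two-sided alpha 0.05, power 95%, 21 per arm (section 4.1); 1:1 allocation (section on randomisation); 30 per arm randomised with 25% allowed for loss (section 4.1). With two MRI time points, the arm-by-time test in a repeated-measures ANOVA is the same as a two-sample t test on change, so t-test power applies.

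**Step 1: reproduce the plan's figure.** Standardised effect d = 0.7/0.6 = 1.167. Noncentrality = d × √(n/2). At n = 21 per arm this is 1.167 × √10.5 = 3.78 on 40 degrees of freedom, and the exact noncentral-t power is 95.8%. At n = 20 it is 94.9%. So 21 per arm is the smallest size reaching 95%, and the 42 comes from 0.7/0.6.

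**Step 2: check the MMSE statement.** If the effect were 2 points with the stated SD of 0.6, d = 2/0.6 = 3.33 and 4 per arm would suffice. For 21 per arm to be the 95% answer for 2 points, the SD would have to be about 1.75. The article gives no MMSE SD, so the 42 was not derived from MMSE.

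**Step 3: look for the inputs that the primary test needs.** These are the expected between-arm difference in 12-month change and the SD of that change. The article gives neither, nor a reason to carry 0.7 and 0.6 over to change. No single corrected power can be computed.

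**Step 4: show how much it matters.** All differences and correlations below are assumptions. If the SD of volume is 0.6 at both visits and ρ is the correlation between them, SD of change = 0.6 × √(2(1 − ρ)). This gives 0.60 for ρ = 0.50, 0.27 for ρ = 0.90 and 0.12 for ρ = 0.98. Power at 21 per arm, with 30 per arm in brackets:

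| Difference in change | SD 0.60 | SD 0.27 | SD 0.12 |
|---|---|---|---|
| 0.10 cm3 | 8% (10%) | 22% (30%) | 75% (89%) |
| 0.20 cm3 | 18% (25%) | 65% (81%) | over 99% |
| 0.35 cm3 (half of 0.7) | 45% (60%) | 98.5% (99.9%) | over 99% |

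**Step 5: what the fixed size can detect without those assumptions.** With 25% loss, 30 × 0.75 = 22.5, so 22 evaluable per arm. Solving the same power function for d:

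- 22 per arm: 0.865 SD of change at 80% power, 1.113 SD at 95%.
- 30 per arm: 0.74 SD at 80%, 0.95 SD at 95%.

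**The case against.** A reader might infer that the trial is underpowered, or that the primary test does not have 95% power. The document does not support that. The two inputs are both wrong in kind, and replacing them may move power in opposite directions: the true difference in change may be well below 0.7 cm3, but the SD of change may also be well below 0.6. No passage makes 0.10 or 0.20 cm3 the expected effect, and the table contains favourable cells as well as poor ones. Nor is 21 per arm the only relevant size: 30 per arm are randomised, and at 0.20 cm3 with SD 0.27 that raises power from 65% to 81%. This objection stands, and it limits the conclusion to power that is not established.

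Two further points carry some weight. The cited study is not at hand, and section 4.1 does not say which of the groups differ by 0.7 cm3. That the figure is a cross-sectional difference between diagnoses is an inference from the wording, though the article offers no other reading. Also, section 4.3 commits to a 95% confidence interval for the difference in change, which would show the imprecision of a null result, and the defect biases neither the test nor the estimate. That reduces the harm but does not make the stated power correct.

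The statistical analysis plan or full protocol may say more, but this is not a matter of omitted detail. The article states the inputs, their source and the resulting power, and as stated they do not match the primary comparison.

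**Conclusion.** The concern holds in this form: the arithmetic is right, but the 95% power was calculated for a between-diagnosis difference in hippocampal volume and is not established for the between-arm difference in 12-month change. Actual power cannot be verified from the article. Across the assumed differences and SDs in the table it ranges from 8% to over 99% at 21 per arm, so the stated figure gives no usable guide. The reading of 0.7 and 0.6 as between-diagnosis quantities rests on section 4.1's own description of the reference study. The bound on the effect rests on the slowing or stabilisation objective in section 2.1.1. The reference to 2 MMSE points is a separate inconsistency in the same section and gives the 42 no alternative basis.

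**What to change.** Keep 60 patients and rewrite section 4.1 on the scale of the primary test:

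- Withdraw the claim of 95% power based on 0.7 cm3 and SD 0.6.
- State what the fixed size detects in SDs of 12-month change: about 0.87 (0.865) at 80% power and 1.11 at 95% with 22 evaluable per arm; 0.74 and 0.95 with 30 per arm.
- Convert these to cm3 only with a sourced SD of 12-month change in hippocampal volume, and add a sensitivity range labelled as assumptions. An SD built from the between-person 0.6 and an unsourced correlation should not be written in as fact.
- Remove the 2-point MMSE difference, or justify it separately with an MMSE SD and its own calculation.
- Reword the hypothesis as a smaller reduction in hippocampal volume than with placebo.

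The cost is wording in the protocol and the analysis plan, plus a search for a usable SD of change. No patients are added. The downside is that the stated power may become less favourable.

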#### 2.1.3. Primary Endpoint

The volume (mm^3^) of the hippocampus, entorhinal cortex and neocortex and the dilation of lateral ventricles determined from T1-weighted MRI will be analyzed at 12-month intervals. Treatment will be deemed successful if atrophy of the areas is significantly lower than that of the control group at 12 months. Cognitive impairment will be measured using the MMSE scale at the final visit compared to baseline, and treatment will be successful if MMSE is significantly higher than that of the control group at 12 months

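### The sample size of 42 is calculated from hippocampal volume but reported as detecting 2 MMSE points, so the 95% power stated for MMSE has no derivation

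*Protocol article*

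**What the plan says.** Section 4.1 of the protocol article opens by stating that "the estimation of sample size is based on the variation in the volume of the hippocampus". It takes its effect and variability from a reference study of hippocampal volume in diagnostic groups, where "the mean difference in these groups was 0.7 cm^3^ with a maximum standard deviation of 0.6". It then sets the error rates ("Fixing α = 0.05, β = 0.05 (i.e., power = 95"%), the variability ("SD = 0.6 (chosen as the higher value observed in the reference study") and the test ("conducting a two-sided t test"). The conclusion of that same sentence is that "42 patients (i.e., 21 patients in each arm) are sufficient for detecting a difference of 2 points in MMSE".

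Two other places bear on this. Section 2.1.3, headed Primary Endpoint, lists the imaging volumes and then adds that "treatment will be successful if MMSE is significantly higher than that of the control group at 12 months". Section 4.3 specifies a treatment comparison by name only for the change in hippocampal volume.

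**The concern.** The calculation goes in with cubic centimetres and comes out with points on a cognitive scale. Nothing in the article links the two: no MMSE standard deviation is given anywhere, and the 2-point difference has no source. Either the sample size belongs to hippocampal volume and the named effect is wrong, or it belongs to MMSE and the inputs are wrong.

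This is the plan's only statement of what the trial can detect and with what power. Because MMSE carries its own success rule under the primary endpoint, a reader may reasonably take the trial as having 95% power for 2 MMSE points. A non-significant MMSE result could then be read as good evidence against an effect of that size, when the true power is unknown.

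**Working it through.** **Inputs from section 4.1:** difference Δ = 0.7 cm³; SD σ = 0.6; two-sided α = 0.05; power 95%; two-sample t test. Allocation is 1:1 (Randomization section). Stated result: 21 per arm, 42 in total. Stated detectable effect: 2 MMSE points.

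**Step 1. Reproduce the plan's figure from the volume inputs.**

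Normal approximation: n per arm = 2 × [(z₀.₉₇₅ + z₀.₉₅) × σ/Δ]² = 2 × [(1.960 + 1.645) × 0.6/0.7]² = 19.1, rounded up to 20.

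The exact calculation (noncentral t) with standardised effect d = 0.7/0.6 = 1.167 gives 20.1, rounded up to 21 per arm, or 42 in total. Power is 94.9% at 20 per arm and 95.8% at 21. This matches the stated figure exactly. A one-sided test would give 17 per arm and does not match.

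**Step 2. Try the MMSE effect with the only SD given.**

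d = 2/0.6 = 3.33. The normal approximation gives 2 × [(1.960 + 1.645) × 0.6/2]² = 2.3, rounded up to 3. The exact calculation gives 3.6, rounded up to 4 per arm (power 97.3%; 3 per arm gives 85.7%). The stated 21 per arm does not come from this reading.

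**Step 3. Find the SD that would make the MMSE statement true.**

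Solving the exact power function for 95% power to detect 2 points gives SD = 1.75 at 21 per arm and SD = 2.11 at 30 per arm. Neither value appears in the document.

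**Step 4. Show how MMSE power depends on the missing SD.** The SDs below are assumptions, since the document gives none. The difference is 2 points, two-sided α is 0.05, and the test is the exact t test.

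| Assumed SD of analysed MMSE quantity | Power, 21 per arm | Power, 30 per arm | n per arm for 95% power |
|---|---|---|---|
| 1.5 | 98.8% | 99.9% | 16 |
| 2.0 | 88.5% | 96.8% | 27 |
| 2.5 | 71.6% | 86.1% | 42 |
| 3.0 | 55.9% | 71.9% | 60 |
| 3.5 | 43.9% | 58.6% | 81 |

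**The case against.** The strongest reply is that the calculation is sound and only one phrase is wrong. The volume inputs reproduce 42 exactly, section 4.1 says at its outset that hippocampal volume was used, and section 4.3 names that variable for the treatment comparison. The primary objective (2.1.1) covers imaging only, and cognition sits among the secondary objectives (2.1.2). A careful reader might therefore treat the MMSE phrase as a drafting slip, and correcting it changes neither the sample size nor the analysis.

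Most of that is fair: the number 42 is not in dispute for the volume inputs. But the slip falls on the sentence that states the detectable effect, and section 2.1.3 gives the reader a reason to take it at face value.

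A second reply is that the loss of MMSE power rests on assumed SDs. Entry requires an MMSE of at least 24 and a CDR of 0.5, and the SD in such a group might be small; at 1.5, power at 21 per arm would be 98.8%. This stands. A shortfall is possible but not shown. What is shown is that the claim has no derivation.

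A third reply is that restoring 0.7 cm³ does not by itself establish power for the planned analysis, because that figure is described as a difference between diagnostic groups and not as a treatment difference in 12-month change. That is true, but it is a separate question and does not rescue the MMSE statement.

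**Conclusion.** The concern holds. The detectable effect in section 4.1 is wrong as written: 21 per arm follows from a hippocampal difference of 0.7 cm³ with SD 0.6, and 2 MMSE points do not follow from those inputs under any reading. This conclusion needs no outside figure.

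The practical size of the error depends on an SD the document does not give. The 95% claim for MMSE would be true at 21 per arm only for an SD up to about 1.75, and at 30 per arm only up to about 2.11. Over the assumed range of 2.0 to 3.5, power runs from 88.5% to 43.9% at 21 per arm and from 96.8% to 58.6% at 30. The sentence must be corrected because it is the plan's only power statement and it attaches to a success rule listed under the primary endpoint.

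**What to change.** In section 4.1, replace the MMSE phrase with the hippocampal-volume difference actually used, stating its units and what it represents (a difference between groups in volume, or between arms in 12-month change). Remove the implied 95% power for MMSE. If the investigators want to report MMSE power, add a separate sentence giving it over a range of explicitly stated SDs for 12-month MMSE change, with a source for the SDs and for the 2-point difference. Carry the same wording into the SAP, which section 4.3 says will be finalised before the database is frozen.

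The cost is one corrected sentence in each document. No patients are added and no analysis changes. The plan gives up a power claim for MMSE that it cannot at present support; whether the replacement figure is lower depends on the SD.

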### 4.2. Methods

All the variables will be descriptively analyzed by treatment and visit (mean, median, standard deviation, interquartile range for continuous variables, frequency distribution for categorical variables). Efficacy analysis will be applied in all populations. Results from the ITT (Intention To Treat) population will be considered the primary ones.

Analyses will be performed using SPSS by the Statistician in charge of this study (different from the above-mentioned Independent Statistician). The statistical significance level chosen is equal to 0.05.

